## Abstract

**Aim:**

To assess the feasibility and acceptability of a virtual reality-based nature intervention in long-term care facilities and explore psychosocial effects ahead of a future randomised controlled trial.

**Design:**

Two-centre feasibility study in a mixed-methods design, focusing on qualitative evaluation.

**Methods:**

Ten residents and ten nursing staff members from two long-term care facilities complete twelve 15-minute virtual reality sessions using a 360° forest video developed by the study team. Over four weeks, residents conduct three sessions each week. Six residents receive support by nursing staff once weekly. The primary outcome feasibility will be qualitatively assessed through semi-structured interviews and qualitative content analysis. Secondary outcomes, including sleep quality, anxiety, depressive symptoms, wellbeing, loneliness and trust in nursing staff, will be analysed using quantitative descriptive analysis.

**Conclusion:**

The study will provide insights into the feasibility of implementing virtual reality-based nature interventions in long-term care, informing a full-scale effectiveness trial.

**Impact:**

The feasibility study will provide information about the barriers and facilitators of the VR-based nature intervention for long-term care facility residents and nursing staff. This information will offer valuable insights into the feasibility of VR interventions in long-term care settings for (workplace) health promotion. Information about the potential effectiveness of the Nature-Boost VR intervention will offers useful perspectives for adapting and improving similar interventions.

**Reporting method:**

This protocol (Version 1.0) complies with the SPIRIT-Outcomes 2022 and TIDieR checklist.

**Patient and public involvement:**

Residents and nursing staff contribute feedback to refine the intervention.

**Clinical Trial Registration:**

https://drks.de/search/en/trial/DRKS00037568/details, identifier DRKS00037568.

## What does this paper contribute to the wider global clinical community?

This protocol introduces immersive virtual nature into everyday care routines, offering a low-barrier, relationship-focused mental health intervention for populations with limited access to natural environment (e.g., geriatrics, palliative care, neurorehabilitation).By fostering trust and strengthening nurse-patient relationships, the intervention addresses a key global challenge in long-term care: maintaining quality relationships despite staff and time constraints.The outlined feasibility framework provides a template for international adaptation of virtual nature interventions across diverse healthcare systems.It challenges the clinical community to reimagine the therapeutic landscape of long-term care by merging cutting-edge technology with deeply human needs: connection, calmness, and presence.

## Introduction

1

The United Nations estimates the global population aged 65 years and older will more than double from 727 million in 2020 to 1.5 billion by 2050, accounting for 16.0% of the global population (1). Meanwhile, according to the World Health Organization (WHO), there will already be a shortage of approximately 4.5 million nurses in 2030 (2). As a result, the number of people requiring long-term care is likely to rise, while the number of available care workers is declining, widening the gap between care needs and personnel resources. This imbalance increasingly limits the time available for individual attention and contributes to higher levels of stress and increased burnout rates among staff (3).

This development may also affect the residents of long-term care facilities, as the achievable quality of care depends, among other things, on the nurse-to-patient-ratio and the amount of time nursing staff can dedicate to each resident (4). Simultaneously, many residents have extensive care needs related to activities of daily living due to advanced age, limited mobility and complex geriatric conditions (5). As a result, residents may experience fewer social interactions and reduced sensory stimulation, which in turn increases the risk of affective impairments, loneliness, cognitive decline, and sleep disorders. Sleep disturbances can further heighten the risk of cognitive deterioration and increase mortality risk, for example through an increased risk of falls and strokes (6–9).

Beyond basic care provision, the quality of the nurse-patient relationship plays a critical role in residents' overall well-being. However, under conditions of staff shortages, it becomes increasingly difficult to build and maintain stable, trust-based relationships, largely due to limited time and attention (10). A strong nurse-patient relationship has been associated with improved physical and emotional well-being in care-recipients (11–13). Trust is often described both as prerequisite for and an outcome of such a strong nurse-patient relationship (14).

These developments underline the need for feasible, preventative and health promoting interventions that can be integrated into everyday life and care to support both residents and nursing staff under structural constraints. Within this context, nature-based interventions offer a promising candidate approach, as they combine low-threshold exposure to restorative environments with potential psychological and physiological benefits. Nature-based interventions, such as forest therapy and forest bathing [Shinrin-yoku, introduced by Tomohide Akiyama in Japan in 1982 (15)], have been associated with psychological restoration and improved (mental) wellbeing (16, 17). Further studies (18–22) suggest reductions in mental disorder, depressive, anxiety, and stress-related symptoms following exposure to natural environments. Some studies have also reported physiological indicators of relaxation, such as changes in blood pressure, cortisol, or prefrontal activity (23). This evidence provides a broader rationale for the restorative potential of nature exposure.

The Attention Restoration Theory posits that modern life demands, such as sustained focus at work, can lead to mental fatigue through overuse of directed attention. In contrast, nature-based interventions may engage involuntary attention through soft fascination, allowing the brain's executive system to rest and recover (24). A randomised controlled trial (RCT) by McDonnell & Strayer supported this theory by showing that nature walks lowered frontal midline theta activity in EEG which was interpreted as reflecting restoration of executive attention (25). Similarly, a systematic review by Song et al. (2016) found that nature-based interventions lowered the absolute haemoglobin concentrations in the prefrontal cortex, indicating relaxation (19). Notably, even isolated sensory stimuli, such as the scent of Hinoki cypress leaf oil, have been shown to elicit comparable effects (26). Hence, Attention Restoration Theory provides one theoretical explanation for why natural environments may support psychological restoration.

However, for many individuals with limited mobility, such as residents in long-term care facilities, direct access to natural environments is often not feasible (27). In such cases, technological alternatives may offer partial access to nature's sensory stimuli. Studies have shown that even viewing photographs or videos of natural landscapes, especially forests, can induce physiological relaxation by reducing sympathetic nervous system activity (28, 29). Additionally, a decrease in perceived loneliness was reported in an online survey conducted during the COVID-19 pandemic after participants watched nature videos (30). Building on these findings, digital nature interventions using virtual reality (VR) offer an even more immersive experience by using realistic, customisable 360° videos, providing nature experiences that can be tailored to individual preferences, without the need for physical relocation. Both healthy individuals and those with mental health conditions have shown improvements in stress, anxiety, and depressive symptoms following exposure to this form of digital nature-based intervention (31, 32).

The present feasibility study focuses on psychosocial and relational domains that are highly relevant for residents in long-term care. Wellbeing, loneliness, affective symptoms, and sleep quality are closely interconnected in older adults. These outcomes are influenced by social isolation, reduced social participation, mobility limitations, and environmental factors that restrict opportunities for meaningful engagement and stimulation (33–35). VR-based nature exposure may provide a low-threshold opportunity for distraction, soft fascination, relaxation, and positive emotional engagement within the care setting (32, 36, 37). In addition, when sessions are conducted jointly with nursing staff, the shared experience may provide an opportunity for interpersonal connection and may enhance the nurse-patient relationship and the residents' perceived trust in nursing staff. In addition, when sessions are conducted jointly with nursing staff, the shared experience may provide an opportunity for interpersonal connection and may enhance the nurse-patient relationship and the residents' perceived trust in nursing staff.

In the present feasibility study, the Attention Restoration Theory informs the conceptual rationale for using immersive VR-based forest exposure in long-term care. The primary goal of VR-based nature interventions is to provide visual nature experiences to long-term care residents despite mobility limitations, thereby supporting their well-being and potentially preventing outcomes such as sleep disturbances, affective disorders, loneliness, and reduced trust in nursing staff. The study focuses on feasibility, acceptability, and implementation in routine care, while exploratory questionnaire data will describe changes in sleep quality, anxiety and depressive symptoms, subjective wellbeing, loneliness, and trust in nursing staff.

Figure 1 illustrates the assumed pathways of the VR-based nature intervention. The immersive forest videos are expected to provide a restorative nature experience through soft fascination, attentional restoration, relaxation, distraction, and perceived presence. These processes may contribute to exploratory changes in sleep quality, anxiety and depressive symptoms, subjective wellbeing, and loneliness. In joint sessions with nursing staff, the shared VR experience may additionally support interpersonal connection and trust in nursing staff. The primary focus of the present study is feasibility and acceptability, including adherence, barriers and facilitators, safety, and implementation within long-term care routines.

**Figure 1 F1:**
[figure not shown]
Conceptual framework of the nature boost feasibility study.

*Nature Boost* aims to examine the acceptance, feasibility, influencing factors and potential barriers of VR-based nature interventions in long-term care facilities in Germany. Given that older adults often have limited experience with VR technology, this preliminary evaluation is crucial. Identifying any challenges in implementation will help optimise the design of the subsequent RCT, which aims to assess the intervention's effectiveness.

## The study

2

The overall aim of the study is to assess the feasibility and acceptance of a VR-based nature intervention in long-term care facilities from the perspectives of nursing staff and residents, and to explore potential effects on health and well-being.

### Primary objective

2.1

To evaluate the feasibility and acceptability of implementing a VR-based nature intervention in long-term care facilities from the perspectives of residents and nursing staff.

### Secondary objectives

2.2

To identify barriers to implementation from the perspectives of residents and nursing staff.To assess changes in the nurse-patient relationships resulting from joint sessions.To explore potential effects of the intervention on sleep quality, mood, subjective well-being, feelings of loneliness among residents, and trust in nursing staff.

These outcomes address challenges that are especially common among long-term care residents and have previously been shown to benefit from nature-based interventions in prior studies (18, 20).

### Research questions and exploratory objectives

2.3

The feasibility study *Nature Boost* will be conducted using a parallel mixed-methods design with a qualitative focus (38). The exploratory research design gives rise to the following qualitative research questions:
How is the use of VR-based nature interventions in long-term care facilities perceived by residents and nursing staff in terms of acceptance and feasibility?What specific barriers to implementation are reported by residents and nursing staff?How does the interventions shape the nurse-patient relationship?What additional potentials are reported in the interviews by residents and nursing staff?

For the quantitative strand of the study, the following exploratory research question is formulated: Can descriptive changes in sleep quality, anxiety and depressive symptoms, subjective well-being, loneliness, and trust in nursing staff be observed over the course of the VR-based nature intervention? Due to the exploratory nature of the feasibility study, no fixed efficacy endpoints are defined. Instead, the qualitative research questions and exploratory quantitative objective will be investigated in an open-ended manner to inform the design of a future effectiveness trial.

## Methods

3

The pilot study employs a parallel mixed-methods design (see Figure 2), with a focus on the qualitative component (38). This mixed-methods approach was chosen to explore both the participants' subjective experiences, the feasibility of the intervention, and to get first insights into potential effects of the intervention. The quantitative component will be used to assess the feasibility, completeness, participant burden, and suitability of the selected outcome measures. Descriptive changes in questionnaire outcomes will be interpreted cautiously and used to identify promising outcome domains for a future effectiveness trial. The design of a subsequent RCT will additionally be informed by feasibility parameters from the present study, clinically meaningful target differences, and evidence from the wider literature. The combination of qualitative and quantitative research strands allows the exploration of contextual factors and barriers that may arise during the following RCT and are not captured through quantitative data alone. Specifically, the impact of the implementation in different long-term care facilities and if residents are able to conduct sessions independently will be analysed.

**Figure 2 F2:**
[figure not shown]
Study design overview. A parallel mixed methods design with qualitative focus is implemented. Orange boxes mark the qualitative, blue boxes the quantitative research strand. The dotted line represents the overlap of both strands during sampling. Semi-structured qualitative interviews form the qualitative, questionnaires the quantitative assessment. Integration of both strands will be conducted in the interpretation phase to enable a comprehensive exploration of the research aim. Illustration based on Kuckartz (39).

### Setting

3.1

To identify contextual factors, the intervention will be implemented in two long-term care facilities in Berlin, Germany. The selection of two facilities from different socioeconomic areas is intended to capture variation in implementation context. Facility-level socioeconomic context may influence feasibility through several pathways, including differences in institutional resources, staffing routines, residents' previous exposure to digital technologies or nature-based activities, health literacy, mobility limitations, and the amount of support required during the VR sessions. These contextual factors may affect how acceptable, accessible, and practical the intervention is in everyday care and will therefore be explored qualitatively as potential influences on implementation.

### Intervention

3.2

In both facilities, participants engage with immersive 360° forest videos, developed by the research team. The videos will be shown using Meta Quest 3S VR headsets (non-medical device). The forest shown in the videos represents a typical German mixed woodland and is intended to evoke a familiar environment for participants. Twelve different videos of forest walks were produced. Participants watch three 15-minute videos per week over a four-week period. They can freely look around during each session.

The VR intervention was developed by the research team to provide a low-threshold audiovisual approximation of a forest walk for residents with limited access to natural environments. The videos were filmed during walks through Schorfheide-Chorin UNESCO Biosphere Reserve in autumn using the INSTA360 X3 Actioncam 360° camera. Each video consists of a continuous recording without cuts to preserve the perceived flow of walking through the forest. The camera operator walked at a slow and steady pace intended to be suitable for older adults. The camera was positioned at approximately 180 cm. Audio was captured using the camera's built-in microphone and consists of natural ambient forest sounds, including wind, birdsong, and footsteps on the forest floor.

The intervention engages participants primarily through visual-spatial immersion and auditory stimulation. Participants can freely look around during the 360° video, creating a sense of presence within the forest environment. Real-world forest exposure remains a broader multisensory experience, and future adaptations may explore additional sensory components.

Before implementation in the long-term care facilities, the videos and technical procedures were reviewed by members of the research team as well as two external research associates with experience in nature-based interventions and two students not affiliated with the project and without former VR experience. This preliminary testing focused on technical functionality, usability, tolerability, perceived image and sound quality, and the suitability of video duration and pacing. Feedback from this phase was used to refine the video selection and implementation procedures before use in the real-world care setting.

Five out of 10 residents will complete one VR session per week together with a member of the nursing staff^1^. The participating staff member may vary between sessions depending on shift schedules, workload, and availability. This approach reflects real-world long-term care routines, where residents are commonly supported by several members of the nursing team. Accordingly, trust is conceptualized as residents' perceived trust in nursing staff more broadly. The qualitative interviews will explore how residents and nursing staff perceive the joint sessions, including whether shared VR experiences influence interpersonal connection, perceived support, and trust in nursing staff under routine care conditions.

The remaining four residents will conduct the sessions independently following an initial briefing and instructions from nursing staff. Residents receive a personal VR headset for the duration of the intervention and complete the sessions before bedtime in an upright position in bed or another seated position.

The VR system is preconfigured to minimise handling steps. Specifically, the VR headsets will be fully configured by the research team before use. Residents are not expected to navigate the standard Meta Quest menu or select videos independently. Instead, the respective intervention video will be preselected and started by nursing staff after instruction. Thus, residents only need to wear the headset and experience the video, while technical handling is kept to a minimum. For joint sessions, nursing staff will use shared VR headsets, which require a short calibration phase before each session.

At the beginning of the intervention period, an information session with hands-on training is held with participating residents and nursing staff to explain the use of the VR headsets, outline the course of the intervention, and address any questions. Usual care and daily routines within the long-term care facilities, regular medication, therapeutic procedures and social activities may continue unchanged during the intervention period.

After each use, the VR headsets and contact surfaces will be cleaned and disinfected according to the facility's hygiene standards.

After each session, the intervention will be documented in an individual intervention diary, noting the session date, duration, whether the session took place individually or in a resident-nursing staff dyad, whether a nursing staff member was present, and any relevant comments. This diary is developed and provided by the research team to help track the sessions and will be explained to participants prior to the intervention.

If participants are not able to complete a session, the next session will be supported by a nursing staff member, including a repetition of the technical instructions if needed. The reason for the missed or incomplete session should be documented in the intervention diary. The intervention was described according to the TIDieR checklist (Appendix).

### Sampling

3.3

A total of 20 participants, including residents (*n* = 10) and nursing staff (*n* = 10) who meet the inclusion criteria (see Table 1), will be recruited from the two long-term care facilities. Given the exploratory study design, no formal sample size calculation was conducted, as this sample size is expected to provide sufficient depth of data and a broad range of perspectives to explore the key feasibility objectives. We retain the option to expand the sampling at a later stage, if needed.

**Table 1 T1:** Inclusion and exclusion criteria.

Inclusion criteria	Exclusion criteria
Residents	
Leaves care home ≤1x per week	Contraindications to the use of VR technology (severe balance disorders, epilepsy)
Living in a long-term care facility at least for the time of the intervention and interviews	Participation in a similar study within 12 months
Sufficient physical and mental ability to participate in the intervention [turn the head to explore the VR-simulation, independent (dis-) mounting of the headset]	Physical or mental conditions that impair participation in the intervention or data collection (mild & severe cognitive deficit, not compensable severe visual or auditory impairments)
	Impaired ability to give consent due to physical or mental limitations
	Medical devices sensitive to magnetic fields (pacemakers, defibrillators, special hearing aids and VP shunts)
	Severe psychiatric disorder (psychotic disorder, bipolar disorder)
Nursing staff	
German language proficiency of at least B2^a^	Contraindication to the use of VR technology (severe balance disorders, epilepsy)
	Participation in a similar study within 12 months
	Time-related limitations that interfere with study participation (e.g., planned holiday, shift plan)

Participation in similar study that exclude from this study are other virtual reality-based interventions or structured psychological programs that may influence mood, sleep, well-being, anxiety or depression.

a According to the Common European Framework of Reference for Languages (CEFR).

Recruitment will be initiated through gatekeeper, such as care facility management and staff representatives, who will be contacted via email, followed by a phone call or an in-person meeting to introduce the study. Informational flyers will be distributed and displayed within the facilities. The recruitment of residents and nursing staff will take place in close coordination with facility management and nursing staff, who propose eligible participants based on the eligibility criteria. Nursing staff may also volunteer to participate in the study.

For an overview of the participant timeline, see Figure 3.

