**Figure 3 F3:**
[figure not shown]
Participant timeline. The inclusion to the study includes an eligibility screening, the informed consent to participate and the qualitative purposeful sampling to intervention groups. Blue boxes mark quantitative and orange boxes qualitative assessment. The time points for data collection are: before the start of the intervention (T0), 2 weeks after the start (T1) and after the end of the intervention (T2).

All participants will be selected according to maximal variation sampling criteria to ensure a broad perspective on the research questions (40).

Maximal variation sampling will be applied pragmatically within the eligible pool available in the two participating facilities. The aim is to include a range of perspectives that are relevant for assessing feasibility and acceptability in a real-world long-term care setting. For residents, variation will be sought with regard to age, gender, and degree of mobility. For nursing staff, variation will be sought with regard to age, gender, and work experience. The exact number and socio-demographic composition of eligible residents and staff will depend on the participating facilities and will be documented during recruitment. Basic information on the available recruitment pool and the socio-demographic characteristics of included participants will be reported in the feasibility study.

Afterwards, residents will be assigned into two groups, aiming for an equal distribution of characteristics:
(1)“Residents completing a weekly VR session together with a nurse” and(2)“Residents conducting the sessions independently after initial instruction”.

In the joint sessions, nursing staff actively participate by watching a 360° video with the VR headset together with the resident. In addition, they may provide support if the resident encounters difficulties with the device or procedure. Including participants from two separate facilities as well as the variation between individual and joint sessions with nursing staff allows the exploration of contextual variability. The sample is adequate to inform adjustments to the study design and intervention for a subsequent RCT.

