### Data collection

3.4

Data collection will be conducted on site at each pilot facility. Questionnaires will be administered at three time points: baseline (T0), two weeks after the start of the intervention (T1), and after completing the intervention (T2). Semi-structured interviews will be conducted post-intervention phase (T2) in a quiet, one-on-one setting to ensure privacy and minimise disturbances.

At baseline, basic socio-demographic and health-related characteristics will be collected to describe the sample and contextualize feasibility findings. For residents, these will include age, gender, duration of residence in the long-term care facility, degree of mobility, frequency of leaving the facility, relevant sensory limitations, previous experience with VR or similar digital technologies, and selected health information relevant to participation, such as contraindications to VR use and relevant physical or cognitive limitations. For nursing staff, baseline characteristics will include age, gender, professional role, years of professional experience, duration of employment in the facility, and previous experience with VR or similar digital technologies.

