### Ethics and dissemination

5.1

The study has been approved by the Ethics Committee of Charité—Universitätsmedizin Berlin (EA4/126/25). Any significant protocol modifications (e.g., changes to eligibility criteria, outcomes or data collection procedures) will be submitted to the Ethics Committee of Charité for review and approval prior to implementation. Relevant changes will also be updated in the trial registration and if applicable, reported in future publications or participant communication materials. Informed consent by the participants of the study will be obtained by members of the research team. Residents will receive both verbal and written information about the study. Written informed consent will be obtained prior to participation. The written consent forms and all study related documents for residents and nursing staff were approved by the Ethics Committee.

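### Table 1 excludes residents, but not nursing staff, with magnetic-field-sensitive medical devices, although staff also wear a VR headset in joint sessions and no reason is given

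*Protocol article*

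**What the plan says.** Table 1 in section 3.3 (Sampling) sets out eligibility separately for residents and nursing staff.

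- **Residents.** Among the exclusions are "Contraindications to the use of VR technology (severe balance disorders, epilepsy") and, in a row of its own, "Medical devices sensitive to magnetic fields (pacemakers, defibrillators, special hearing aids and VP shunts").
- **Nursing staff.** There are three exclusions: "Contraindication to the use of VR technology (severe balance disorders, epilepsy"), "Participation in a similar study within 12 months", and scheduling constraints such as leave or shift plans. None mentions a medical device.

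Staff are participants (10 of the planned 20) and are exposed to the equipment. Section 3.2 (Intervention) says "For joint sessions, nursing staff will use shared VR headsets", and section 3.3 adds that "nursing staff actively participate by watching a 360° video with the VR headset together with the resident". The only headset model named is the Meta Quest 3S (section 3.2).

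On other information gathered from staff, section 3.4 (Data collection) says "For nursing staff, baseline characteristics will include age, gender, professional role, years of professional experience, duration of employment in the facility", plus earlier VR experience. The corresponding list for residents includes contraindications to VR use.

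**The concern.** Some resident-only rows, such as those on cognition or capacity to consent, plausibly reflect who the residents are. The device row is of another kind. Its stated ground is sensitivity to magnetic fields, which depends on the headset and on the implant or aid, not on whether the wearer lives or works in the facility. If the sponsor regards the headset as reason enough to exclude a resident with a pacemaker, the same reasoning applies to a nurse with one.

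What is at stake is the safety of staff participants. Facility management and nursing staff propose candidates against the listed criteria, and staff may volunteer, so the table is the working filter. An omission there carries straight through to who puts on a headset.

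**Working it through.** The article gives no figure to reproduce. The main check is a row-by-row comparison of the two blocks of Table 1.

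| Exclusion | Residents | Nursing staff |
|---|---|---|
| VR contraindication (balance disorders, epilepsy) | yes | yes |
| Recent similar study | yes | yes |
| Magnetic-field-sensitive device | yes | **no** |
| Conditions impairing participation or data collection | yes | no |
| Impaired capacity to consent | yes | no |
| Severe psychiatric disorder | yes | no |
| Scheduling constraints | no | yes |
| **Total** | **6** | **3** |

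Three further readings follow.

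1. *Could the staff VR contraindication row cover devices?* Its parenthesis names two conditions and does not mark them as examples, although the scheduling row in the same block does use an example marker. In the resident block the device row stands beside the same VR row, so the table treats the two as distinct.
2. *Is there another check?* An eligibility screening is shown in the participant timeline (Figure 3), but it can only apply the criteria it is given. Section 5.5 (Monitoring and safety) describes responses to symptoms after exposure and does not mention devices. The staff baseline list has no health item. That last fact is weak support, because the list also omits epilepsy, which is an explicit staff exclusion.
3. *Is a reason stated?* None was found in the article.

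Scale of exposure, using the article's counts:

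- Joint sessions: 5 residents × 4 weeks = 20 (section 3.2), or 6 × 4 = 24 (Abstract, Methods). The article gives both numbers of residents, so both are carried.
- Staff headset time in all: 20 × 15 = 300 minutes to 24 × 15 = 360 minutes.
- Per staff member, if spread evenly over 10 (assumption): 20/10 = 2.0 to 24/10 = 2.4 sessions, or 30 to 36 minutes.
- Number of affected staff (assumption, as the documents give none): 0 gives 0 sessions; 1 gives 2.0 to 2.4; 2 gives 4.0 to 4.8.

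These figures describe exposure, not risk.

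**The case against.** The strongest reply has four parts.

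- **The general criterion suffices.** A screener could count a pacemaker as a contraindication to VR if the headset instructions say so. This is possible, but it relies on the screener going beyond the listed conditions, and the resident block shows that the authors thought a separate row was needed.
- **The hazard is not shown.** The article does not say that the headset produces a relevant field, or at what distance. The device manual, screening form and information sheets are not at hand. This stands: what is established is an unexplained omission, not a demonstrated danger. It does not help that the article condenses a fuller protocol, because the article prints criteria for both groups, repeats one row for staff and leaves out the other.
- **Exposure differs.** Residents have 12 × 15 = 180 minutes with a personal headset, against an estimated 30 to 36 minutes for staff. This is a real difference, but the device criterion carries no exposure threshold, and the article does not offer the difference as a reason. The staff estimate also leaves out any headset use during the hands-on training, and an uneven shift pattern would put more sessions on some staff.
- **The weight is small.** Perhaps no one is affected, and adverse event monitoring covers all participants. The first part may be true. The second acts only after exposure and does not replace an exclusion.

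**Conclusion.** The concern holds. Two groups wear VR headsets, one is screened for magnetic-field-sensitive devices and the other is not, and the article gives neither a reason nor another safeguard before exposure. The two blocks do not contradict each other; the staff block has a gap.

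The effect is confined to staff who have such a device. Their number is unknown and may be zero. For each of them the planned exposure is about 2.0 to 2.4 sessions, assuming an even spread over 10 staff. No harm is shown, and no outcome, estimate or analysis changes. The conclusion rests on Table 1 being the operative list of criteria and on staff using equipment to which the resident criterion would equally apply. It should be corrected because it concerns safety and the correction is cheap.

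**What to change.** Add the resident row, "Medical devices sensitive to magnetic fields (pacemakers, defibrillators, special hearing aids and VP shunts"), to the nursing staff block of Table 1, and put the same device question to staff at the eligibility screening. Section 5.1 states that significant modifications (such as "changes to eligibility criteria, outcomes or data collection procedures) will be submitted to the Ethics Committee of Charité for review and approval") need approval before implementation, so the change goes through that route. Until it is approved, no staff member with such a device should wear a headset. If the team has a sound reason for treating staff differently, stating it in section 3.3 would also close the gap.

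The cost is one table row, one screening question and a short amendment. The downside is possibly one staff candidate fewer, and staff must disclose a health item. The research team, not facility management, should therefore ask the question.
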